# Intravenous Ascorbic Acid for the Prevention of Postreperfusion Syndrome in Orthotopic Liver Transplantation: Protocol for a Randomized Controlled Trial

**DOI:** 10.2196/50091

**Published:** 2023-12-15

**Keywords:** antioxidant therapy, antioxidant, ascorbic acid, blood, controlled trials, hepatic, ischemia, ischemic, liver transplantation, liver, postreperfusion syndrome, randomization, randomized controlled trial, RCT, reperfusion injury, reperfusion, surgery, surgical, transplant, transplantation, vascular, vitamin C, vitamin, vitamins

## Abstract

**Background:**

Liver transplantation is the last therapeutic option for patients with end-stage liver disease. Postreperfusion syndrome (PRS), defined as a fall in mean arterial pressure of more than 30% within the first 5 minutes after reperfusion of at least 1 minute, can occur in liver transplantation as a deep hemodynamic instability with associated hyperfibrinolysis immediately after reperfusion of the new graft. Its incidence has remained unchanged since it was first described in 1987. PRS is related to ischemia-reperfusion (I/R) injury, whose pathophysiology involves the release of several mediators from both the donor and the recipient. The antioxidant effect of ascorbic acid has been studied in resuscitating patients with septic shock and burns. Even today, there are publications with conflicting results, and there is a need for further studies to confirm or rule out the usefulness of this drug in this group of patients. The addition of ascorbic acid to preservation solutions used in solid organ transplantation is under investigation to harness its antioxidant effect and mitigate I/R injury. Since PRS could be considered a manifestation of I/R injury, we believe that the possible beneficial effect of ascorbic acid on the occurrence of PRS should be investigated.

**Objective:**

The aim of this randomized controlled trial is to assess the benefits of ascorbic acid over saline in the development of PRS in adult liver transplantation.

**Methods:**

We plan to conduct a single-center randomized controlled trial at the Hospital Universitario Ramón y Cajal in Spain. A total of 70 participants aged 18 years or older undergoing liver transplantation will be randomized to receive either ascorbic acid or saline. The primary outcome will be the difference between groups in the incidence of PRS. The randomized controlled trial will be conducted under conditions of respect for fundamental human rights and ethical principles governing biomedical research involving human participants and in accordance with the international recommendations contained in the Declaration of Helsinki and its subsequent revisions.

**Results:**

The enrollment process began in 2020. A total of 35 patients have been recruited so far. Data cleaning and analysis are expected to occur in the first months of 2024. Results are expected around the middle of 2024.

**Conclusions:**

We believe that this study could be particularly relevant because it will be the first to analyze the clinical effect of ascorbic acid in liver transplantation. Moreover, we believe that this study fills an important gap in the knowledge of the potential benefits of ascorbic acid in the field of liver transplantation, particularly in relation to PRS.

**Trial Registration:**

European Union Drug Regulating Authorities Clinical Trials Database 2020-000123-39; https://tinyurl.com/2cfzddw8; ClinicalTrials.gov NCT05754242; https://tinyurl.com/346vw7sm

**International Registered Report Identifier (IRRID):**

DERR1-10.2196/50091

## Introduction

### Scientific Background and Explanation

The first liver transplant (LT) in the world was performed in 1963 [1], but the first successful transplant was carried out by [name] at the University of Pittsburgh in 1967 [2]. Until the introduction of immunosuppression with cyclosporine in the early 1980s, the survival rate of transplanted patients remained at 20% [3,4]. The 1-year and 5-year patient survival rates have increased to 85% and 70%, respectively, due to advances in surgical and anesthetic techniques and immunosuppression protocols. Despite these advances, hemodynamic changes during surgery remain a challenge for anesthesiologists.

One of the most serious changes during LT can occur at the time of graft reperfusion as an adverse hemodynamic situation known as postreperfusion syndrome (PRS), first described by Aggarwal et al [5] in 1987. They defined PRS as a deep and transient cardiovascular collapse immediately after graft reperfusion, with severe bradycardia, decreased mean arterial pressure (MAP) and systemic vascular resistance, severe arrhythmias, increased pulmonary artery pressure and central venous pressure, and even cardiac arrest. They defined it as a decrease in MAP of more than 30% within the first 5 minutes of graft reperfusion lasting at least 1 minute. The development of PRS is associated with decreased survival, an increased incidence of postoperative renal failure, early graft dysfunction, and the need for blood product transfusion in the setting of severe fibrinolysis [6-8]. Although it was first described in 1987, its incidence has not decreased over the past decades, ranging from 8% to 35% [9-11].

The intrinsic mechanisms of PRS are complex and not fully understood. Several theories have been proposed, including an abrupt accumulation of factors upon reperfusion, such as metabolic acidosis, hyperkalemia, hypokalemia, hypothermia, air emboli, and the release of vasoactive and proinflammatory mediators from both allograft and recipient, which are responsible for decreased systemic vascular resistance and myocardial depression [1,12-19]. During perfusion of the new graft, many proinflammatory cytokines are released from the new liver, such as tumor necrosis factor alpha and interleukins (ILs; IL-1, IL-2, and IL-8), and others from the patient (kallikrein and bradykinin). Other mediators have been found to be elevated after reperfusion (arginase, endotoxins, thromboxane, and monocyte chemoattractant protein-1), but the role of each of these mediators in the onset and severity of PRS is not known [18,20-24].

Ischemia-reperfusion (I/R) injury in LT is associated with graft dysfunction and decreased survival, but its exact role in PRS is controversial. I/R results in cell death due to lack of oxygenation, which occurs during the ischemic period and is exacerbated immediately after reperfusion by the release of proinflammatory cytokines and oxygen free radicals, activation of the complement system leading to sinusoidal vasoconstriction, and local hemoconcentration in the graft with the presence of neutrophils and platelets. All these mechanisms exacerbate the systemic inflammatory response (vasodilation and myocardial depression). The extent to which I/R contributes to the development of PRS and the severity of hemodynamic abnormalities is not entirely clear [25,26], but it seems logical to conclude that PRS is another manifestation of I/R injury. Several randomized controlled trials have been published using different drugs to prevent the onset of PRS (methylene blue, acetylcysteine, antifibrinolytics, and others). However, none of these have shown a beneficial effect.

On the other hand, there has recently been renewed interest in the use of high-dose vitamin C as a supportive treatment in patients with severe septic shock (metabolic resuscitation) [27]. Sepsis has been shown to decrease the levels of some vitamins, such as ascorbic acid, which has been associated with the development of multiorgan failure and death. Intestinal absorption of vitamin C is saturable, so the only way to increase its levels would be by intravenous administration. Tanaka et al [28] reduced resuscitation fluid volumes in patients with burns by administering high doses of intravenous ascorbic acid. This was a randomized controlled trial of 37 patients allocated to receive a dose of 66 mg/kg/hour of vitamin C versus saline during the first 24 hours of resuscitation. Although MAP and central venous pressure were similar at the end of the vitamin C or saline infusion, fluid administration was lower in the intervention group, and patients maintained higher urine output and developed less wound edema with a significant reduction in the duration of mechanical ventilation (12 days vs 21 days; *P*=.03).

Zabet et al [29] investigated the effect of high doses of vitamin C on vasopressor requirements in septic shock. As ascorbic acid is required for catecholamine synthesis [30], it was investigated whether it could be useful in shortening vasopressor weaning. A total of 24 patients with vasopressor-dependent septic shock were randomized to receive vitamin C at a dose of 25 mg/kg intravenously every 6 hours versus saline. The dose and duration of vasopressors were significantly reduced in the intervention group, as was mortality.

The most important study in septic patients was conducted by Marik et al [31], who used a combination of hydrocortisone, ascorbic acid (1.5 g every 6 hours), and thiamine (200 mg every 12 hours) in 47 patients with sepsis admitted to the intensive care unit with procalcitonin levels >2 ng/mL. The aim of thiamine was to prevent kidney oxalate accumulation. Mortality decreased in patients treated with vitamin C (*P*<.001). They were weaned from vasopressors earlier and received less intravenous fluid for resuscitation than the control group.

Vitamin C is safe even in very high doses. Fowler et al [32] conducted a safety study of intravenous ascorbic acid in 24 patients with severe sepsis (low dose 12.5 mg/kg every 6 hours vs high dose 50 mg/kg intravenously every 6 hours). No adverse events were observed. No adverse effects were reported in any of the above studies, including the study by Tanaka et al [28], in which the doses were very high (1.6 g/kg over 24 hours). Metabolism of vitamin C to oxalic acid could theoretically cause calcium oxalate nephropathy. However, this does not seem to be a real problem, as renal toxicity is dose-dependent and has only been reported at very high doses (>40 g/day) [33]. In addition, coadministration of thiamine would reduce the conversion of vitamin C to oxalate. In the study by Marik et al [31], the incidence of renal failure requiring renal replacement therapy was significantly lower in the intervention group (33% vs 10%; *P*=.02).

However, several meta-analyses have been published in recent years with mixed results. In most of them, a reduction in mortality, duration of mechanical ventilation, and hospitalization could not be demonstrated. However, a reduction in the sepsis-related organ failure assessment score and a shorter duration of treatment with vasoactive drugs is a common finding [34-38].

I/R injury plays a pivotal role in the development of graft dysfunction after liver transplantation, and excessive free radical production and massive depletion of endogenous antioxidants are common mechanisms underlying I/R injury. Ascorbic acid is an essential micronutrient involved in the antioxidant response and modulation of apoptosis and inflammation. These properties may, therefore, make it a potential strategy for reducing I/R injuries. In addition, its safety profile, low cost, and ease of administration favor its use in this scenario [39]. As discussed above, we can consider PRS as one of the clinical manifestations of I/R injury. Therefore, if we can prevent or at least attenuate I/R injury, we may be able to reduce the incidence of I/R injury.

### Aim

The aim of the study is to determine the possible benefit of vitamin C in reducing the incidence of PRS in liver transplantation.

## Methods

### Study Setting

The trial has been designed in accordance with the updated CONSORT (Consolidated Standards of Reporting Trials), the Declaration of Helsinki, and the Good Clinical Practice guidelines issued by the Spanish regulatory authorities. The study will be conducted at a single center, the Hospital Universitario Ramon y Cajal in Madrid (Figure 1).

**Figure 1 figure1:**
[figure not shown]
CONSORT (Consolidated Standards of Reporting Trials) flow diagram.

### Trial Design

This study is designed as a single-center, double-blind, randomized controlled trial. Participants will be randomized to receive ascorbic acid (intervention group) or saline (0.9%; control group). We will conduct a superiority analysis.

### Eligibility Criteria for Participants

All patients over 18 years of age who are on the waiting list for liver transplantation may be eligible to participate in this study. The inclusion and exclusion criteria are detailed in Textbox 1.

Inclusion and exclusion criteria.
**Inclusion criteria**
Aged between 18 and 67 yearsWaiting for a liver transplantNegative pregnancy test in women
**Exclusion criteria**
PregnancyAllergy to ascorbic acidNephrolithiasisGlucose-6-phosphate dehydrogenase (G6PD) deficiencyHyperoxaluriaHyperuricemiaHaemochromatosisSickle cell anemiaSerum creatinine >1.2 mg/dL (women) and 1.3 mg/dL (men)Split liver graftAcute liver failureLiving donor liver transplantationGrafts from donation after circulatory deathTreatment with indinavir, vitamin B_12_, cyclosporine, iron, deferoxamine, or disulfiram

### Study Procedures and Intervention

The intervention group will receive a dose of 1500 mg of intravenous ascorbic acid (vitamin C) diluted in 100 mL of 0.9% saline for 30 minutes, to be administered during the anhepatic phase of liver transplantation.

The control group will receive a dose of 100 mL of 0.9% saline for the same period and under the same conditions.

### Outcome Measurements

The primary end point of the study is the percentage of patients who develop PRS after liver graft reperfusion. PRS is defined as a 30% decrease in MAP within the first 5 minutes after portal-clamp release that persists for at least 1 minute.

Textbox 2 contains the secondary variables that are also analyzed.

Secondary variables.
**Secondary variables**
The percentage of patients with primary failure and early graft dysfunction. Primary graft failure is defined as the complete absence of liver graft function. The patient will not survive without retransplantation. In the case of early graft dysfunction, patient survival is likely and possible without retransplantation, although morbidity will be greater than in the case of normal function. The following Olthoff criteria are used for its definition (one criterion is enough):Bilirubin ≥10 mg/dL on postoperative day 7.International normalized ratio ≥1.6 on postoperative day 7.Alanine aminotransferase or aspartate aminotransferase >2000 IU/mL in the first 7 postoperative days.Length of stay in the intensive care unit and hospitalization. The number of days spent in the surgical intensive care unit and the total number of days spent in the hospital.Dose and duration of catecholamines from the time of reperfusion.Length of time on mechanical ventilation (hours). Time to extubation of the patient.Vitamin C levels before transplantation and 12 hours after transplantation. Measurements are performed by high-pressure liquid chromatography with an ultraviolet detector.Levels of inflammatory markers (IL-1β, tumor necrosis factor alpha, IL-6, IL-8, and IFN-γ) before and after transplantation as measured by the high-sensitivity enzyme-linked immunosorbent assay technique.Development of postoperative kidney failure (acute kidney injury [AKI]) during the first week. AKI is defined as an increase in serum creatinine (SCr) ≥0.3 mg/dL within 48 hours or an increase in SCr × 1.5 times baseline; known or presumed to have occurred within the previous 7 days.Need for postoperative renal replacement therapy during the first week. Need for any type of renal replacement therapy during the first 7 days after transplantation, regardless of the technique used.Graft and patient survival 30 days after transplantation.

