### Participant Timeline

Patients will be monitored from randomization until day 30 post surgery. The team will collect variables daily through postoperative day 7 and a final visit on postoperative day 30. The research team will closely monitor adverse events, including onset, duration, intensity, progression, and outcome, to assess their relationship to the drug.

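### The transaminase cut-off for early graft dysfunction is printed per millilitre, a level no patient would plausibly reach; probably a unit slip, to be corrected before analysis (minor)

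*Protocol article*

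**What the plan says.** The protocol article, under Outcome Measurements, lists the secondary variables in Textbox 2. One of them is "The percentage of patients with primary failure and early graft dysfunction". Primary failure has its own description in words. Early graft dysfunction is defined by a named, published set of three laboratory criteria, with the rule that "one criterion is enough":

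- "Bilirubin ≥10 mg/dL on postoperative day 7"
- "International normalized ratio ≥1.6 on postoperative day 7"
- "Alanine aminotransferase or aspartate aminotransferase >2000 IU/mL in the first 7 postoperative days"

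The transaminase threshold appears nowhere else in the article, so no other section confirms or corrects its unit. On data capture, the Participant Timeline section says: "The team will collect variables daily through postoperative day 7".

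**The concern.** The third criterion is a decision threshold. Because any one criterion is sufficient, it can classify a patient without the other two. Stated per millilitre, the cut-off is 1000 times the same number stated per litre, and it lies far outside any level a serum transaminase could be expected to reach.

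If the text were followed exactly, the criterion would classify nobody. The other two criteria are read on day 7 only, whereas the transaminase criterion spans the whole first postoperative week. Losing it would remove the only part of the definition that can register an event before day 7. A patient who qualified through transaminases alone would be recorded as having no early dysfunction. That would carry into the comparison of arms, because the Analysis section applies its procedure for the primary outcome to the secondary efficacy analyses as well.

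**Working it through.** **Inputs**

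- Cut-off: more than 2000 IU/mL, alanine or aspartate aminotransferase (Textbox 2).
- Combination rule: any one of three criteria (Textbox 2).
- Conversion: 1 L = 1000 mL.
- Highest transaminase value in a recipient: not in the document. Assumed peaks run from 2,000 to 50,000 IU/L, with the upper end meant as extreme.

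The cut-off is a chosen definition and does not derive from other figures in the article, so there is no plan figure to reproduce.

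**Step 1. Convert the printed cut-off.**

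2000 IU/mL × 1000 mL/L = 2,000,000 IU/L.

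**Step 2. Compare assumed peaks with it.** Fraction of the cut-off = peak ÷ 2,000,000.

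| Assumed peak (IU/L) | Same value in IU/mL | Fraction of printed cut-off | Criterion met? |
|---|---|---|---|
| 2,000 | 2 | 0.1% | No |
| 5,000 | 5 | 0.25% | No |
| 10,000 | 10 | 0.5% | No |
| 20,000 | 20 | 1% | No |
| 50,000 | 50 | 2.5% | No |

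The margin at the extreme end is 2,000,000 ÷ 50,000 = 40. The assumed maximum would have to be wrong by a factor of more than 40 before a single patient qualified.

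**Step 3. Compare with a per-litre reading.** If the intended unit is IU/L, the cut-off is 2000 IU/L = 2 IU/mL, a factor of 1000 below the printed value. Every assumed peak above 2,000 IU/L would then qualify.

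**Step 4. Effect on the outcome if the printed unit is applied.** Let *s* be the share of true early-dysfunction cases that qualify by transaminases only. Then

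recorded rate = true rate × (1 − *s*).

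The article gives neither the true rate nor *s*. In principle *s* can lie anywhere from 0 (every such patient also meets the bilirubin or INR criterion) to 1 (none does). The direction is therefore known, since the recorded rate cannot exceed the true one, but the size cannot be estimated from the document.

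**The case against.** The strongest reply is that nothing in the trial need have gone wrong. The textbox names a published criteria set, so the intended standard is identifiable. A slip in a journal textbox does not show that the case report form or the derivation code carries the same unit, and neither is shown. Misclassification also needs a particular sequence: someone takes results reported per litre, converts them to per millilitre, compares them with 2000, and does not notice that no patient comes near. The Analysis section says SPSS will be used and describes no such conversion. If the laboratory reports per litre and the reported number is simply compared with 2000, patients are classified as they would be under a per-litre cut-off.

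This stands as a limit on the consequence. It does not make the printed definition correct: it only says that staff may apply a definition different from the published one.

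A reader might also infer more than the document supports:

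- *That the criterion is inoperative in the trial as run.* It is inoperative only if the printed unit is applied literally, and nothing shows that it has been.
- *That the under-count can be quantified.* The article gives neither the dysfunction rate nor the share qualifying by transaminases alone.
- *That the component most specific to ischemia-reperfusion injury is lost.* The Introduction links that injury to graft dysfunction in general and does not rank transaminases above bilirubin or INR.
- *That the result is biased towards one arm.* The same cut-off applies to both arms, and nothing in the article shows a difference between them in how often it would matter.
- *That the outcome must be redone for the 35 patients already recruited.* The Results section places data cleaning and analysis in the first months of 2024, so there is no sign that it has yet been derived.

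**Conclusion.** The criterion is wrong as written, and the point is minor. The conversion to 2,000,000 IU/L is exact. That no patient would reach this level rests on an assumption about serum values, but the conclusion holds across the whole assumed range, with at least a 40-fold margin.

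The most likely explanation is a unit slip. If the printed unit were applied literally, early graft dysfunction would depend on day-7 bilirubin and INR alone. The separately described primary graft failure would be unaffected. If staff compare per-litre laboratory results directly with 2000, the data are unaffected and only the published text needs correcting.

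The reach is one of three components of one secondary outcome. The primary endpoint, the sample size and the significance level do not depend on it. Confidence is high that the unit is misprinted; there is no evidence that any patient has been misclassified.

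**What to change.** 1. Check the transaminase unit against the cited criteria and against the unit in which the hospital laboratory reports (assumed here to be per litre), and correct Textbox 2 accordingly.
2. Before analysis, confirm that the case report form and the derivation code use that same unit.
3. Re-derive early graft dysfunction only if the printed unit was actually applied to any patient.

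The cost is one unit in the text and a short check of the form and the code. No new data are needed, because variables are already collected daily over the period concerned. With analysis planned for early 2024, the correction can come first.

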### Participant Timeline

Patients will be monitored from randomization until day 30 post surgery. The team will collect variables daily through postoperative day 7 and a final visit on postoperative day 30. The research team will closely monitor adverse events, including onset, duration, intensity, progression, and outcome, to assess their relationship to the drug.

